***Secondary endpoints***

*1. Mortality*

Mortality at 8- and 24-weeks post randomisation will be compared between study arms.

*2. Time to normalization of conscious level*

We will determine days from randomisation until observation of a GCS of 15 which is achieved for ≥2 consecutive days.

*3. Functional status*

The modified Rankin scale at 8 and 24 weeks will be used in determining functional outcomes.

*4. TB immune reconstitution inflammatory syndrome*

TB-IRIS will be diagnosed according to published case definitions
^31^. TB-IRIS will be determined independently by 2 trial clinicians blinded to treatment allocation.

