^12^. Currently, little is known about rifampicin concentrations in brain matter, spinal cord or meninges and how plasma levels or inflammation affect tissue concentrations.

The evidence for the currently recommended dose of rifampicin (10mg/kg/day) in TBM treatment is scant, and this dose falls on the steep part of the dose-response curve for sterilising effect
^27^. Recent studies by the Pan-African Consortium for the Evaluation of Antituberculous Antibiotics in pulmonary TB have shown that rifampicin dosed at 35mg/kg is associated with improved early bactericidal activity and 2-fold faster rate of sputum conversion (Hazard Ratio 1.99, 95% CI:1.21-3.29) as compared to standard therapy. Furthermore, this dose was safe and well tolerated, with a 14% grade 3-5 adverse event incidence as compared with 10% with standard 4-drug TB therapy with rifampicin dosed at 10mg/kg
^28^.

Ruslami
*et al*. investigated the safety and pharmacokinetic (PK) profiles of higher than normal dose
*intravenous* (IV) rifampicin as well as oral moxifloxacin in adults with TBM. Although not powered to detect a mortality benefit, improved survival was observed in patients receiving 600mg IV rifampicin (~13mg/kg/day) compared to the oral standard dose (~10mg/kg/day). Patients who received IV rifampicin had a more rapid resolution of coma (4 versus 5 days), reduced mortality at 8-weeks (24% versus 55%) and 6-months (34% versus 65%); (adjusted Hazard Ratio=0.42; 95% CI 0.20-0.91, p=0.03) compared with those who received oral standard dose rifampicin. The change in rifampicin dose and mode of delivery was associated with a 3-fold increase in plasma area under the time-concentration curve (AUC) and maximum concentration (C
_max_) and a 3-fold increase in CSF C
_max_ from 0.21 to 0.60 mcg/mL.

A second phase II study in Indonesia evaluating increased
*oral* doses of 30mg/kg or 20mg/kg versus standard of care (10mg/kg) also reported no increase in toxicity in the high dose arms and CSF C
_max_ was significantly increased (25.5 mg/L [11.9 to 55.5], 18.1 mg/L [2 to 43.6], 7.2 mg/L [2.2 to 14.1] respectively, <0.001). In those with microbiologically confirmed TBM there was a trend towards lower 6-month mortality in the 30mg/kg arm compared to standard of care (7% versus 36% (HR 0.16 [0.02 to 1.34], p=0.09)
^29^.

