**Control arm, standard of care arm (R10PO)**

The control arm will receive standard of care TB treatment: Oral rifampicin ~10 mg/kg, isoniazid ~5 mg/kg, pyrazinamide ~25 mg/kg, ethambutol ~20 mg/kg in fixed-dose combination tablets according to weight bands for 8 weeks (
Table 4). Participants will receive intact tablets or via nasogastric tube. Fixed dose combination antituberculous therapy will be prescribed through routine care pathways initially via the hospital and subsequently via at TB clinics according to National Guidelines.

***Pharmacokinetic sampling.*** Intensive plasma PK sampling will take place on day 2(+/-1) at hours 0, 2, 4 and 8 post dose as well as a single CSF sample. Where possible a single plasma and CSF sample will be collected on day 14 (+/- 2 days).

***Blood test monitoring.*** Routine blood monitoring will take place on days 1, 3, 7 and 14, week 4 and week 8 to monitor for any rifampicin-related toxicity (
Table 5 and
Table 6).

**Table 5. T5:** In-patient schedule of events.

Study visit	Screening	Enrolment D1	Day 2	Day 3	Day 7	Day 10	Day 14	Further Hospitalization
Visit window (days)			±1	±1	±1	±1	±2	
Screening Consent	X							
Assess eligibility criteria		X						
Informed enrolment consent		X						
Clinical history and examination								
Past medical history	(X)							
Medication review	(X)	X	X	X	X	X	X	X
Document HIV status	(X)							
Current symptoms	(X)	X	X	X	X	X	X	X
Examination	(X)	X	X	X	X	X	X	X
GCS score	(X)	X	X	X	X	X	X	X
BMRC disease grade		X	X	X	X	X	X	X
Adverse events assessment ^b^		X	X	X	X	X	X	X
Investigations								
HIV-test (if not known positive)	(X)							
Cryptococcal antigen	(X)							
Sodium/Potassium	X ^i^	X ^i^			X		X	X
Glucose (bedside)	(X)							
Creatinine ^h^	X ^i^	X ^i^			X		X	X
Hepatic panel ^a^	X ^i^	X ^i^		X	X		X	X
Blood Count (including differential)	X ^i^	X ^i^			X			X
CD4 count if HIV-positive	X ^i^	X ^i^						
Pregnancy test	Women							
CSF sample (aim >10ml, as per SOP ^c^)	(X)		X ^d^	as clinically indicated (storage of remaining specimen)			X (Paired plasma)	X (as clinically indicated)
Plasma PK sampling 0, 2, 4, 8 hrs			X					
Sparse plasma PK (one sample)							X	
Chest radiograph	(+/-)							
CT head ^f^	+/-	+/-						
Abdominal Ultrasound Scan		X						
Urine sample ^g^	(X)							
Blood/DNA/RNA storage		with consent						with consent
Approx. volume blood (mL)	0	20	20	3	7	0	7	7

**()**= part of routine medical care

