### Data collection

***Baseline and subsequent assessment.*** Participants will be followed as in-patients for the first 14 days and then approximately 4 weekly as outpatients until week 24, see
Table 5 and
Table 6. If a trial participant dies during the in-patient period additional consent will be sought from family members for a post-mortem examination to explore cause of death and levels of rifampicin in brain tissue. Recruitment will continue for 12–18 months with an additional 6 months follow-up period. The trial will be considered closed when the last participant has completed 24 weeks in the study, all SAEs resolved and all follow-up and laboratory reports have been received.

***Data handling and data management.*** Source documents are made up of detailed case report forms (CRFs), laboratory results, radiology results and other relevant documents. Data entry will occur via the DataFax system, whereby the paper-based case record forms are scanned, emailed to a server, and data entered by intelligent character recognition. After an initial automated error-checking, secondary review for accuracy is then performed by the DataFax team at the Infectious Diseases Institute, Uganda. The DataFax system allows for automated data queries to alert for any missing data on an ongoing basis. Second, this also allows for permanent archiving and potential remote review by oversight bodies. Study forms will be harmonized between all study sites enabling multi-site data management. The investigator will retain study essential source documents for 20-years after the completion of the study, as per Ugandan guidelines. Digital images of the source documents will be retained for an indefinite period.

***Quality control and assurance.*** Site monitoring is conducted to ensure that the human subject protection, study procedures, laboratory, study intervention administration, and data collection processes are of high quality and meet the sponsor, ICH E6 and regulatory guidelines. The study may be subject to audit by the London School of Hygiene & Tropical Medicine under their remit as Sponsor, as well as other regulatory bodies to ensure adherence to Good Clinical Practice.

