**Clinical outcomes**

Survival at 8 and 24 weeks will be calculated using the risk difference, from a generalised linear regression model adjusted for site and BMRC TBM grade. Kaplan-Meier curves will also be used to compare time to death between treatment arms, with censoring and loss to follow-up handled as previously described. Cox proportion hazards regression will be used to assess the effects of rifampicin dose, plasma/CSF rifampicin concentration, HIV, MRC severity grade and baseline GCS on survival.

When calculating time to normalization of GCS continuous-valued secondary endpoints will be compared with general linear models or Wilcoxon rank-sum tests as appropriate. Death can be considered a competing risk. χ
^2^ test will be used for comparison of proportions of patients with TBM-IRIS by intervention arm.

***Secondary analysis.*** We will explore the relationship between rifampicin exposures and clinical outcomes using a population pharmacokinetic-pharmacodynamic model. We will consider C
_max_ and AUC
_0-24h_ as the exposure variables. Survival, proportion with normalisation of conscious level and functional status (as determined by modified Rankin score) are the response variables.

***Planned subgroup analyses.*** Specified high-risk subgroups are of interest because of potential different responses to intravenous rifampicin from both an efficacy and safety perspective, and the clinical utility in future physician decision-making. With standard therapy, worse clinical outcome is associated with altered mental status, high organism burden. Subgroups of interest include:

1. TBM Diagnostic category (Definite, Probable, Possible)
^33^
2. British Medical Research Council (BMRC) TBM disease severity
^7^
3. CSF inflammation (CSF white blood cells) by tertiles4. CD4 at study entry5. ART status at study entry

***Analysis of ancillary studies.*** The results of ancillary studies will be reported separately from the main trial.

Findings of the diagnostic sub-study will be reported in line with the Standards for the Reporting of Diagnostic Accuracy studies (STARD) guidelines. Sensitivity and specificity will be calculated against a composite reference standard (any positive CSF test for
*M. tuberculosis*) and against the published uniform case definition of ‘probable’ or ‘definite’ TBM
^33^. A latent class analysis will also be performed.

The studies on brain tissue concentration at autopsy will be primarily descriptive.

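### After day 3 the scheduled GCS visits do not by design support a recovery endpoint of two consecutive days, and the tests named for it leave death before recovery unhandled

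*Protocol article*

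**What the plan says.** **Definition.** Protocol article, Secondary endpoints, item 2, measures "days from randomisation until observation of a GCS of 15 which is achieved for ≥2 consecutive days". No restriction to participants with impaired consciousness at entry is stated.

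**Schedule.** The columns of Table 5 are "Study visit Screening Enrolment D1 Day 2 Day 3 Day 7 Day 10 Day 14 Further Hospitalization", and its GCS row reads "GCS score (X) X X X X X X X": one score per listed visit. The windows are ±1 day for days 2, 3, 7 and 10, and ±2 days for day 14. The last column has no stated frequency. Table 6 (out-patient schedule) has no GCS row. Data collection says: "Participants will be followed as in-patients for the first 14 days and then approximately 4 weekly as outpatients until week 24". Nowhere does the article state that GCS is scored daily.

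**Analysis.** Clinical outcomes says: "When calculating time to normalization of GCS continuous-valued secondary endpoints will be compared with general linear models or Wilcoxon rank-sum tests as appropriate". The next sentence allows, but does not require, death to be treated as a competing risk, and attaches no method. By contrast, the Safety analysis section commits to death as a competing risk and names cumulative incidence functions and a Cox model adjusted for site and BMRC grade.

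**Context.** Faster resolution of coma appears in both the secondary hypotheses and the secondary objectives. The background cites coma resolution at 4 versus 5 days in the earlier intravenous rifampicin trial.

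**The concern.** There are two separate mismatches.

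1. **The definition needs scores on consecutive days, and the schedule mostly does not supply them.** A participant first seen at GCS 15 on day 7 has no scheduled score on day 8. The sites would then have to leave the endpoint unmet, stretch the definition, or fall back on unscheduled ward scores. Each choice gives a different recovery date.
2. **The named tests need a number of days for everyone.** A participant who dies without recovering has none. If such participants are left out, the arms are compared within a group selected after randomisation by survival and recovery. In a disease with mortality this high, a regimen that lowers mortality keeps more late recoverers in its own comparison and can look slower to restore consciousness.

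**Working it through.** The article gives no power or event figure for this endpoint, so there is none to reproduce. The mortality planning figures used below do reproduce. With 20 per arm, control survival 0.40 and hazard ratio (HR) 0.285, survival in the better arm is 0.40^0.285 = 0.770. Expected deaths are 20 × 0.60 + 20 × 0.230 = 16.6, and one-sided Schoenfeld power is 0.82 (0.80 with 19 per arm), against 80% stated in Sample size.

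**Step 1: which scheduled visits can be one day apart** (days and windows from Table 5)

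| Visit pair | Nominal gap (days) | Window combinations | Combinations one day apart |
|---|---|---|---|
| 3 and 7 | 4 | 3 × 3 = 9 | 0 (smallest gap is day 4 to day 6) |
| 7 and 10 | 3 | 3 × 3 = 9 | 1 (days 8 and 9) |
| 10 and 14 | 4 | 3 × 5 = 15 | 1 (days 11 and 12) |

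Only the pairs 1–2 and 2–3 are consecutive as scheduled.

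**Step 2: resolution around 4 versus 5 days.** On nominal days, recovery on day 4 and recovery on day 5 are both first seen at the day 7 visit. With windows, a day 3 visit held on day 4 could catch the former, while day 5 lies outside every window.

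**Step 3: upper bound on control times lost to death.** The Abstract gives in-hospital mortality of 44%: 20 × 0.44 = 8.8. Sample size assumes 40% control survival at 8 weeks: 20 × 0.60 = 12. So the bound is about 9 to 12 of 20. It is a bound because some participants recover and die later.

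**Step 4: an estimate under stated assumptions.** Assume exponential times, everyone impaired at entry, the same recovery hazard in both arms, and median recovery of 5 or 20 days (assumed; the article gives no figure). The hazards per day are:

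- control death: −ln(0.40)/56 = 0.01636
- death at HR 0.285: 0.00466
- recovery: ln(2)/5 = 0.1386, or ln(2)/20 = 0.0347

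With r the recovery hazard, d the death hazard and F = 1 − exp(−56(r + d)), the chance of recovering before death within 8 weeks is r/(r + d) × F. The median time among those recovered is −ln(1 − F/2)/(r + d).

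| Median recovery | Arm | F | Recovered of 20 | No recovery time, of 20 | Median among recovered (days) |
|---|---|---|---|---|---|
| 5 days | Control | 0.9998 | 17.9 | 2.1 | 4.47 |
| 5 days | Death HR 0.285 | 0.9997 | 19.3 | 0.7 | 4.83 |
| 20 days | Control | 0.943 | 12.8 | 7.2 | 12.5 |
| 20 days | Death HR 0.285 | 0.889 | 15.7 | 4.3 | 15.0 |

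Of the 7.2 controls in the third row, about 6.1 died first and 1.1 were alive but unrecovered. Recovery hazards are equal by construction, yet the recovered-only median is later in the arm with fewer deaths by 4.83 − 4.47 = 0.4 days or 15.0 − 12.5 = 2.5 days. A simulation of 4,000 trials with 20 per arm gave average differences of 0.4 and 2.3 days.

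**Step 5: effect on the test.** In the same simulation the recovered-only Wilcoxon test rejected at the 5% level in 4.7% to 6.3% of trials with death HR 0.285. At this size the bias affects the direction of the estimate far more than the false-positive rate.

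**The case against.** The strongest reply is that this is a journal article. Table 5 lists study visits. Participants are in hospital for the first 14 days, with observed dosing by ward or nursing staff, so GCS may well be charted daily under the full protocol or the case report forms. The windows and the open-ended hospitalisation column also allow some consecutive-day scores. A pre-specified analysis plan is mentioned and could supply a worst-rank rule for deaths, a baseline restriction, or a competing-risk model. The endpoint is one of four secondary endpoints, the modified Rankin scale among them, and carries no power claim.

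Much of this stands, and it rules out several stronger readings that a reader might infer:

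- **That the endpoint cannot be observed after day 3.** Windows, later hospitalisation and ward charting could each supply the second score. The documents show only that the scheduled visits do not do so by design.
- **That a 4 versus 5 day difference would be recorded as zero.** Those figures summarise groups. Two distributions with different centres would still show different proportions recovered by days 3, 7 and 10. Resolution is reduced, not removed.
- **That 9 to 12 of 20 controls would have no recovery time.** That counts every death as a death before recovery.
- **That the plan commits to comparing recovered participants only.** It does not say so; that analysis is one way to fill the gap.

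What the reply does not remove is what the article itself fixes: a definition that its own schedule does not serve, and two tests that do not match the competing risk mentioned in the following sentence. Statistical methods also requires every analysis to be adjusted for site and BMRC grade, which an ordinary rank-sum test does not do.

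**Conclusion.** The point holds in this limited form. The Table 5 visits do not by design support GCS 15 on two consecutive days after day 3: visits 3 and 7 are never adjacent, and the later pairs are adjacent in 1 of 9 and 1 of 15 window combinations. Timing is therefore poor where the cited earlier difference lies. The named tests give no value to those who die unrecovered unless a rule is added, and death is only an optional competing risk.

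Control times lost to death are at most about 9 to 12 of 20 and probably fewer; about 2 to 7 of 20 controls have no time for any reason under the assumptions of step 4. If mortality differed by arm as strongly as HR 0.285, a recovered-only comparison would be shifted by about 0.4 to 2.5 days against the arm with fewer deaths. These figures rest on exponential times, an assumed median recovery of 5 to 20 days and equal recovery hazards. The pharmacokinetic and safety conclusions and the sample size are unaffected.

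**What to change.** 1. **Definition.** Define recovery as GCS 15 at two successive scheduled assessments. Treat its time as interval-censored between the last score below 15 and the first of the two scores at 15. If GCS is already charted daily for in-patients, say so and keep the consecutive-day definition. Either way, state how participants unrecovered at their last GCS assessment are censored, since Table 6 has no GCS row.
2. **Population.** Analyse participants with baseline GCS below 15. The Consent section expects more than 80% to have altered mental status, so fewer than about 12 of 60 (60 × 0.20) would be expected to present with unaltered mental status.
3. **Analysis.** Replace the linear model or Wilcoxon test with the cumulative incidence of recovery, with death as the competing event, and a cause-specific Cox model adjusted for site and BMRC grade. Use a grouped-time form of the model if the visit-based definition is adopted. Make the competing-risk treatment of death a commitment, as the Safety analysis section already does.

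The cost is a change of wording and slightly more analysis work. The visit-based definition also gives a coarser recovery date. No extra participants are needed.

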### Inclusion and exclusion criteria

***Inclusion criteria***. Participants to be included in the study are consecutive patients ≥18 years with clinically suspected TBM based on meningitis symptoms, clinical signs of meningism and anti-tuberculous chemotherapy planned by the attending physician. In addition, they must have either a bedside CSF glucose to plasma ratio <50%, or absolute CSF glucose <40mg/dl or 2.2mmol/l or a positive CSF acid fast bacilli (AFB) smear or positive Xpert MTB/Rif or Ultra. Written informed consent must be given by either by the participant or by surrogate if the participant has altered mental state.

***Exclusion criteria***. Patients with jaundice or known liver cirrhosis will not be eligible to enrol. Additionally, those who have received more than 3 doses of TB treatment within the previous 3 days, or have discontinued TB treatment in the prior 14 days, or those with known allergy to rifamycins, isoniazid, pyrazinamide, ethambutol or study drug excipients are not eligible. Those with known current/previous rifampicin drug-resistant
*M. tuberculosis* infection or those with concurrent cryptococcal meningitis or those known to be currently taking any drug that has a clinically relevant interaction with rifampicin or other first-line TB drugs, including ritonavir, atazanavir or darunavir will not be eligible. Individuals who cannot or are unlikely to attend regular clinic visits or are pregnant or breastfeeding or where we lack consent from participant or family members are not eligible. Those with known porphyria or known chronic renal failure with eGFR <10ml/min are not eligible.

### Randomisation and treatment allocation

Adults who have given consent for, and undergone, a diagnostic screening lumbar puncture and are eligible for enrolment will then be approached for enrolment consent after which they will be randomised. Randomisation will occur at study entry and must occur prior to the 4th dose of TB treatment. Participants will be randomised by a computer generated permutated block randomization algorithm of different sized blocks with a 1:1:1 randomization ratio into the three arms described above.

Randomisation will be stratified by:

1. Clinical site2. British Medical Research Council (BMRC) TBM disease grade I or II/III at time of consent

All randomised participants will initiate their allocated study TB treatment within 24 hours of randomisation, and preferably the same day. As TBM is a medical emergency, initiation of standard of care TB treatment will not be delayed whilst waiting for randomisation.

***Treatment discontinuation***. Due to the urgent need to begin TBM therapy to reduce mortality, enrolment will not be delayed whilst waiting for enrolment blood test results and participants will be replaced
*a posteriori* if baseline ALT>3x ULN. As infection with a rifampicin resistant TB strain is an exclusion criterion, all patients in whom rifampicin resistant TB is identified after randomisation may have their treatment altered as per physician judgement. Once randomised, analysis is by modified intent-to-treat (ITT).

### Interventions

***Diagnostic lumbar puncture***. At the time of screening, after informed consent has been received, a diagnostic lumbar puncture will be performed with a ~10ml CSF sample collected. The sample with then be tested with an enhanced TB diagnostic panel including Xpert MTB/Rif, Ultra, MGIT culture, Biofire meningoencephalitis multiplex polymerase chain reaction and next generation sequencing.

***Antituberculous therapy***

**Intravenous rifampicin arm (R20IV)**

For the first 14 days study drug will be administered as intravenous rifampicin 20mg/kg once daily. Study medications will be dispensed during hospitalization to ward staff who will administer the drugs to the participants under directly observed therapy. Rifampicin 600mg will be reconstituted with 10 ml of sterile water for a dilution of 60 mg per ml of reconstituted solution. The weight-specific volume of rifampicin solution will be drawn up (
Table 1) then further diluted in 500 ml 5% Dextrose solution. The solution will be administered as a continuous infusion via a peripheral venous catheter over 2 hours. Thereafter the line will be flushed with 5 ml 0.9% normal saline after which the cannula will be capped. Other antituberculous drugs (isoniazid, pyrazinamide and ethambutol) will be given orally by weight (
Table 2) as intact tablets unless they are unable to swallow voluntarily, e.g. in participants with a depressed level of consciousness, in which case tablets will be crushed and given via nasogastric tube.

**Table 1. T1:** Intravenous administration of rifampicin by weight for day 0–14 in the intravenous rifampicin arm (arm R20IV).

Weight (Kg)	Rifampicin dose (mg)	SUSPEND RIFAMPICIN IN EACH VIAL (600MG) IN 10MLS OF WATER FOR INJECTION	Volume used (mL)	Number of vials used	DILUTE IN 500MLS OF 5% DEXTROSE AND ADMINISTER OVER 120 MINUTES
28.5 – 31.49	600		10	1.0	
31.5 – 34.49	660		11	1.1	
34.5 – 37.49	720		12	1.2	
37.5 – 40.49	780		13	1.3	
40.5 – 43.49	840		14	1.4	
43.5 – 46.49	900		15	1.5	
46.5 – 49.49	960		16	1.6	
49.5 – 52.49	1020		17	1.7	
52.5 – 55.49	1080		18	1.8	
55.5 – 58.49	1140		19	1.9	
58.5 – 61.49	1200		20	2.0	
61.5 – 64.49	1260		21	2.1	
64.5 – 67.49	1320		22	2.2	
67.5 – 70.49	1380		23	2.3	
70.5 – 73.49	1440		24	2.4	
73.5 – 76.49	1500		25	2.5	
76.5 – 79.49	1560		26	2.6	
79.5 – 82.49	1620		27	2.7	
82.5 – 85.49	1680		28	2.8	
85.5 – 88.49	1740		29	2.9	
88.5 – 91.49	1800		30	3.0	

**Table 2. T2:** Daily number of tablets of isoniazin, pyrazinamide and ethambutol by weight during the first 14 days for the intravenous rifampicin study arm (arm R20IV).

Baseline weight (kg)	ISONIAZID 100 mg*	PYRAZANAMIDE 500 mg*	ETHAMBUTOL 400 mg
≤30–33	1.5	1.5	1
34	1.5	1.5	2
35–44	2	2	2
45–54	2.5	2.5	2
55	3	3	2
56–64	3	3	3
65	3	3.5	3
≥66	3.5	3.5	3

After 14 days of intravenous rifampicin the participant will be switched to high dose oral rifampicin (35mg/kg) for the remaining 6 weeks of the intervention period administered as per the participants in the high dose oral rifampicin arm.

